### Initial screening

The WASI-II has evidence of acceptable validity and adequate reliability.^62^ A clinical neuropsychologist will administer the screener at the screening interview, where both verbal and non-verbal intellectual functioning will be measured. If a recent neuropsychology assessment has been completed (within 12 months prior through the Queensland Paediatric Rehabilitation Service), permission will be sought from the caregiver to share data to avoid unnecessary assessment burden.

Following this appointment, the Behaviour Rating Inventory of Executive Function (BRIEF),^65^ the Conners third edition^66^ and a demographic questionnaire will be completed at T1 to gain information on the cohort characteristics. The BRIEF is an 86-item parent-completed questionnaire that assesses executive function behaviours in the home environment,^65^ while the Conners third edition is a norm-referenced assessment tool used to obtain observations about the young person’s behaviour.^66^ A demographic questionnaire devised for the purpose of the study will be completed by the child’s caregiver. The demographic questionnaire aims to capture sociodemographic information pertaining to each child–caregiver dyad (eg, age and codiagnoses).

### Primary outcome

The Canadian Occupational Performance Measure (COPM)^51^ will be used to assess individual social participation goals over time. The COPM has high test–retest reliability (intraclass correlation coefficient, ICC 0.76–0.89) and is responsive to change. A change of two points or more is considered clinically meaningful.^51^ The COPM will be administered through a semistructured interview with child–caregiver dyads. The goals identified will focus on specific social skills that may assist participants in making and maintaining friendships, such as joining a conversation with a group at school, as well as social participation, like the frequency of get-togethers.

Each child–caregiver dyad will jointly identify 2–3 social goals. The current performance and satisfaction with performance will be rated jointly by child–caregiver dyads using a 10-point numerical rating scale. A rating of 1 indicates poor performance and low satisfaction, while a rating of 10 indicates excellent performance and high satisfaction. At each assessment point, baseline goals will be reassessed; any additional goals will not be formally documented or scored via the COPM. Child–caregiver dyads will receive a copy of their goals; however, they will not have access to the ratings for their goals.

### Secondary outcomes

The SSIS-SEL^52^ is a revised version of the Social Skills Rating System Rating Scales (SSIS-RS),^57^ one of the most routinely utilised questionnaire-based measure of children’s and youths’ social skills.^67^ The SSIS-SEL are a range of questionnaires (student, caregiver and teacher) assessing social–emotional learning skills (ie, social and self-awareness, relationship, responsible decision-making and self-management) in children and youth aged 3–18 years from multiple perspectives.^52^ Test–retest reliability (r=0.73–0.91) and internal consistency for all subscales is high (α=0.89–0.97), with total scale internal consistency estimates comparable between the SSIS-SEL and SSIS-RS.^52^ School-aged children will complete the self-report form, and the child’s primary caregiver will complete the caregiver version of the SSIS-SEL. SSIS-SEL Rating Forms (ie, student, caregiver and teacher) contain 46–51 items, completion time is approximately 10–20 min.

The QPQ by Frankel and Mintz (2011) is a 19-item parent-completed questionnaire that measures the frequency of hosted and invited get-togethers and quality of children’s play during recent playdates on a 4-point Likert scale.^68^ The scale has been utilised as an outcome measure in previous studies testing the efficacy of GSSIs and takes approximately 3 min to complete.^40 41 69^ The QPQ was created through a factor analysis of 175 young people and has a coefficient alpha of 0.87 for the conflict scale. A RCT of PEERS for adolescents revealed a Spearman correlation of 0.55 for the conflict scale and 0.99 for the frequency of hosted or invited get-togethers between parent and youth ratings at baseline (all p’s<0.001).^40^

PECK is a 32-item self-report dimensional assessment of a young person’s experience of being bullied.^54^ The tool has been featured in several evaluations of the effectiveness of bullying prevention programmes. It is suitable for young people aged 8–15 and takes approximately 10 min to complete.^67^ The PECK includes items for four subscales related to relational, physical, cultural and technology-based bullying. Young people are asked how often they have experienced each of the behaviours in the previous month. Responses are rated on a five-point Likert scale, ranging from ‘never’ to ‘most days’.^54^ The PECK has demonstrated good to excellent internal consistency for all four subscales (Cronbach’s alpha range=0.78–0.91; a=0.91 for verbal–relational bullying, a=0.90 for cyberbullying, a=0.91 for physical bullying and a=0.78 for bullying based on culture) and has adequate test–retest reliability (range r=0.61–0.86; r=0.75 for relational verbal bullying, r=0.86 for cyberbullying, r=0.61 for physical bullying, r=0.77 for bullying based on culture).^54^

The TCSSK is an adapted version of the Test of Adolescent Social Skills Knowledge-Revised (TASSK-R).^70^ The 22-item self-report questionnaire will measure a child’s knowledge of the specific skills taught throughout the PEERS Plus programme. The TCSSK takes approximately 5–10 min and requires participants to select the best option from two available answers. Total raw scores range from 0 to 22; a higher total score reflects higher knowledge of social skills. The TCSSK was adapted for use in this research project; accordingly, psychometric properties are not available.

The Caregiver Social Coaching Questionnaire for PEERS (CSCQ for PEERS) is a self-report questionnaire containing 10 items. The CSCQ takes approximately 3–5 min to complete and measures a caregiver’s knowledge, skills and confidence in coaching their child in various social situations and environments. Caregivers’ responses for the 10 items are rated on a Likert scale from 1 (strongly disagree) to 7 (strongly agree). The CSCQ for PEERS was developed for use in this study, psychometric properties have not been investigated.

The KIDSCREEN questionnaires are a series of instruments developed for surveying health-related quality of life (HRQoL) in young people between the ages of 8 and 18.^55^ KIDSCREEN-27 (short version) is a generic measure of HRQoL and has 27 items in five Rasch scaled dimensions: Peers and Social Support, School Environment, Physical Well-Being, Autonomy and Parents and Psychological Well-Being. The measure has shown good scale characteristics (eg, internal consistency; Cronbach’s alpha>70), convergent and criterion validity.^55^ Caregivers will complete the parent proxy version, and school-aged children will complete the self-report form. Estimated completion time is 10–15 min.

The SDQ is a 25-item behavioural screening questionnaire for young people aged 2–17.^56^ The SDQ is divided between five scales, including emotional symptoms, conduct problems, peer relationship problems, hyperactivity/inattention and prosocial behaviour and takes approximately 3–5 min to complete. Caregivers will complete the parent version of the SDQ, which demonstrates strong psychometric properties, including adequate test–retest reliability and internal consistency (*α=*0.80)*.*^71^

The CHU9D is a generic preference-based measure of HRQoL suitable for children and adolescents. The instrument takes approximately 5 min to complete and has nine dimensions (worried, sad, pain, tired, annoyed, schoolwork/homework, sleep, daily routine and able to join activities), each with a range of five possible responses (scored 1–5).^57^ The measure is appropriate for computing QALYs for young people aged 7–17 years; caregivers will complete the parent proxy version.

At the completion of the PEERS Plus programme, a qualitative interpretive description methodology will be employed to capture patterns and themes related to participants’ experiences and perceived acceptability and feasibility of the programme. Interviews will be conducted as focus groups with caregivers and children separately to explore the lived experience of primary and early high school delivered PEERS Plus. All participants will be invited to join the focus groups on programme completion. Semistructured interviews will occur immediately postintervention (ie, session 12) after the completion of all child and caregiver outcome measures/questionnaires to avoid bias. Two semistructured interview guides (ie, a 1 hour caregiver guide and a 20 min child guide) will be used across groups (ie, all immediate and waitlist groups). Interviews will be conducted in person by a researcher who is not involved in the intervention’s delivery, audiotaped and transcribed verbatim. Thematic coding of transcripts will be completed using NVivo software following analysis principles as outlined by Thorne (2016).^72^

### Process outcomes

The number of participants who: (1) are approached for this intervention, (2) commence the programme, (3) complete the programme or (4) decline the programme will be recorded. Reasons for non-participation will be sought and documented. An issues register will be developed to record any technical or logistical difficulties, participant, service delivery or organisational issues.

### Data management

Participants’ data, assessment and administration forms obtained for this research that could identify participants will be deidentified with a coded unique identification number and then stored in a locked filing cabinet at the Queensland Cerebral Palsy and Rehabilitation Research Centre. Data collected and/or uploaded to electronic formats for comparison and analysis will be managed by The University of Queensland through a secure online database.

Group video footage of each session will be transferred to the same secure database by a research team member after each session. Similarly, after the completion of focus group interviews, audio recordings will be uploaded to the same secure database. All information will be treated as confidential and securely stored, adhering to the University of Queensland institutional protocol and the Australian Code for the Responsible Conduct of Research. Final raw trial data will only be accessible to the study investigators or, on reasonable request, made available to other researchers and/or funding bodies, as needed, for the purposes of meta-analysis/systematic review and/or confirmation of statistical results. Identifiable data will not be made available unless separate ethics approval is sought. Aggregated data will be presented at conferences and submitted for publication.

In the event that a participant terminates their involvement in the trial, they will be provided the opportunity to complete outcome measures if applicable. All data will be deidentified prior to the dissemination of results. At the completion of the study, data will be archived as per the Children’s Health Queensland Research Ethics guidelines and institutional protocol.

### Sample size

A total of 32 participants will be recruited to pilot test the PEERS Plus programme. This number will allow for a minimum of 16 participants per group. This sample size will give us 80% power to detect a 2-point difference (clinically meaningful difference)^73^ on the primary outcome, the COPM, assuming a SD of 2^74^ with α=0.05 and buffering for 10% attrition.

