#### Primary hypotheses

For school-aged children (grades 3+; 8–13 years) with ABI or CP, PEERS Plus will be more effective than a waitlist control group receiving usual care to:

Achieve significantly greater self-reported performance of social participation goals as measured on the Canadian Occupational Performance Measure (COPM),^51^ by two points or greater.

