### Management of withdrawals

Before consenting to participate, all participants will be made aware that they are free to withdraw from the study at any time without penalty. Participants who withdraw will not be replaced.

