### Statistical analysis

Analyses will follow standard principles for RCTs, using two group comparisons on all participants on an intention-to-treat basis. Intention-to-treat analysis will be employed to reduce bias and ensure that all participants allocated to either the intervention (PEERS Plus) or control group are analysed together as representing that ‘treatment arm’ whether or not they received the intervention or completed the study.

Summary statistics will be calculated using means and SD or medians and IQR for continuous measures, depending on data distribution. Ordinal data will be summarised using counts and percentages. The approach to handling missing data will depend on its frequency and the underlying factors contributing to its incompleteness. For example, multiple imputation will be used to address missing data when it is believed to be missing at random. Statistical analysis will be conducted using Stata V.18, while qualitative data analysis will be performed using NVivo V.14.

The primary comparison H1 (attainment of social participation goals) immediately post the intervention at 12 weeks will be based on the COPM and will be between treatment groups using generalised linear models. Analyses will use similar methods to compare the outcomes between groups for secondary outcomes and timepoints (social skills and competence, quality of children’s play, the experience of being bullied and HRQoL).

This study will estimate the costs (both direct and indirect) associated with implementing the PEERS Plus programme. This study will adopt micro-costing/bottom-up approach to estimate the average costs of PEERS Plus groups. This costing study will be conducted from the Australian health system perspective, in which direct consumption of resources for providing the PEERS Plus will be measured. The cost analysis will involve a three-stage process: identifying resource use, measurement and valuation. The intervention cost will include consumables required for providing distinct therapy/interventions under the PEERS Plus and time spent by the trainers/therapists to provide in-person sessions to the adolescents and their caregivers. This information will be valuable to policymakers who need to allocate resources for this evidence-based programme.

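### On a two-sided 5% test, 32 children cover the 80% power claim only before attrition; the stated 10% buffer appears only if an undeclared one-sided test was used

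*Protocol article*

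**What the plan says.** The Sample size section of the protocol article sets the total: "A total of 32 participants will be recruited to pilot test the PEERS Plus programme". It continues: "This number will allow for a minimum of 16 participants per group". The power claim follows: "This sample size will give us 80% power to detect a 2-point difference (clinically meaningful difference", on the COPM, "assuming a SD of 2" and "with α=0.05 and buffering for 10% attrition".

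Three other places bear on it:

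- Management of withdrawals: "Participants who withdraw will not be replaced".
- Primary hypotheses: the hypothesis is directional, "PEERS Plus will be more effective than a waitlist control group receiving usual care to" improve COPM performance by two points or more. Neither this section nor any other says whether the test is one- or two-sided.
- Statistical analysis: the primary comparison at 12 weeks "will be between treatment groups using generalised linear models". Baseline COPM is not named as a covariate, and the Sample size section gives no baseline to follow-up correlation.

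**The concern.** A difference of 2 with an SD of 2 is a standardised effect of 1.0. At two-sided 5% and 80% power, the textbook answer is 16 per arm with complete data. That is the number the article recruits, yet the same sentence says 10% attrition has already been allowed for. On the two-sided reading both statements cannot be true of the same 32 children.

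What is at stake is how the trial's sensitivity is described. If the two-sided reading is right, the chance of missing a true 2-point effect after the anticipated loss is about 27% by the t-test, not 20%. A non-significant result would then be read against a power figure that the design does not have.

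**Working it through.** **Inputs.** From the Sample size section: difference 2, SD 2, alpha 0.05, power 80%, 16 recruited per arm, 10% attrition. From Management of withdrawals: no replacement. Sidedness is not given, so both cases are run. The comparison is taken as unadjusted, because no covariate is stated.

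**Step 1: requirement before attrition.** Normal approximation, per arm: n = 2 × (z for alpha + z for power)² × (SD/difference)².

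- Two-sided: 2 × (1.960 + 0.842)² × (2/2)² = 15.7, so 16.
- One-sided: 2 × (1.645 + 0.842)² × (2/2)² = 12.4, so 13.

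The noncentral t-distribution gives 16.7 (so 17) two-sided. One-sided it gives 14, since 13 per arm reaches only 79.7% and 14 per arm reaches 82.4%.

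**Step 2: inflate for 10% attrition, n/(1 − 0.10).**

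| Test | Method | Needed per arm | Divided by 0.9 | Recruit per arm | Total |
|---|---|---|---|---|---|
| Two-sided 5% | Normal | 16 | 17.8 | 18 | 36 |
| Two-sided 5% | t-test | 17 | 18.9 | 19 | 38 |
| One-sided 5% | Normal | 13 | 14.4 | 15 | 30 |
| One-sided 5% | t-test | 14 | 15.6 | 16 | 32 |

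Only the last row gives the plan's own figure of 32 with its buffer. The two-sided normal calculation gives 32 only when the inflation step is left out.

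**Step 3: power of the design as stated.** With 10% loss, 16 × 0.9 = 14.4 per arm remain.

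| Analysed per arm | Two-sided, t-test | Two-sided, normal | One-sided, t-test |
|---|---|---|---|
| 16 | 78.1% | 80.7% | 86.8% |
| 14.4 | 73.4% | 76.5% | 83.4% |
| 14 | 72.1% | 75.4% | 82.4% |

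**Step 4: detectable difference.** At 14.4 per arm, the two-sided t-test has 80% power for 2.17 points, about 2.2.

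**Step 5: effect of adjusting for baseline.** The document gives no correlation, so a range is assumed. With baseline COPM as covariate the residual SD is 2 × √(1 − r²). Two-sided t-test power:

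| Assumed r | 14 per arm | 14.4 per arm |
|---|---|---|
| 0.2 | 73.9% | 75.2% |
| 0.3 | 76.1% | 77.4% |
| 0.4 | 79.4% | 80.5% |
| 0.5 | 83.7% | 84.7% |

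Power returns to 80% at a correlation of about 0.38 (14.4 per arm) to 0.42 (14 per arm).

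**The case against.** A reader might infer that 32 children can reach 80% power only if nobody is lost, so that the buffer is simply false. The document does not support that without a condition. It gives alpha without sidedness and words the primary hypothesis directionally, and a one-sided 5% t-test reproduces both the 32 and the 10% allowance exactly. This part of the objection stands, and it is why the point is conditional. It does not clear the paragraph. No one-sided test is declared, a directional hypothesis is how most superiority trials are worded, and an unqualified 5% is normally read as two-sided. If one-sided was meant, the paragraph omits the assumption on which its result depends.

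A second objection is that the planned generalised linear model may include baseline COPM, a choice often left to the analysis plan. That is possible and would repair the figure at a correlation near 0.4. But the power statement mentions neither adjustment nor correlation, so it cannot be credited with them as written.

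Third, withdrawal from the programme need not mean a lost outcome. The Data management section lets those who stop complete the measures, and multiple imputation is foreseen. Retained assessments would indeed keep the analysed number up. Imputation does not fully recover the information in missing outcomes, so it does not replace a buffer. In any case, the 10% is the authors' own planning figure.

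Fourth, the minimum of 16 per group is most naturally the number recruited. That is a fair reading, and a clarification is enough.

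Finally, this is a pilot with feasibility and acceptability among its aims. That limits the seriousness, but the article still makes a formal power claim for an efficacy hypothesis.

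**Conclusion.** The point holds in conditional form. Either the test is two-sided and the 32 children contain no attrition allowance, or the figure rests on a one-sided 5% alpha that the article does not declare. In the first case, power after 10% loss is about 73% (t-test) or 77% (normal approximation), a shortfall of roughly 4 to 7 percentage points, and the t-test's detectable difference is about 2.2 points instead of 2. In the second case, the arithmetic is sound and the omission is the fault.

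The two-sided figures assume an unadjusted comparison, SD 2, and loss spread evenly over equal arms. It would go too far to conclude that the trial is too small for its purpose or that more children must be recruited: the shortfall is modest, it may vanish with baseline adjustment, and the study is a pilot. This is a should-fix correction to a stated figure.

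**What to change.** Keep 32 and rewrite the Sample size paragraph so that it names the sidedness and the method of calculation. Then take whichever branch applies:

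- **If two-sided:** remove the buffering claim and state that, with 32 recruited and 10% attrition (about 14 to 15 analysed per arm), an unadjusted t-test has about 73% power for a 2-point difference, or 80% power for 2.2 points. Alternatively, base the statement on a baseline-adjusted analysis, say that the primary model includes baseline COPM, and give the assumed baseline to 12-week correlation (about 0.4 restores 80%).
- **If one-sided 5% was used:** declare it, show the step from 14 to 16 per arm, and report the two-sided power beside it.

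In both cases describe 16 per group as the number recruited, not the number analysed. The cost is one reworded paragraph and, in the unadjusted two-sided case, a slightly less favourable stated power. No extra children are needed.

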### Management of withdrawals

Before consenting to participate, all participants will be made aware that they are free to withdraw from the study at any time without penalty. Participants who withdraw will not be replaced.

### Statistical analysis

Analyses will follow standard principles for RCTs, using two group comparisons on all participants on an intention-to-treat basis. Intention-to-treat analysis will be employed to reduce bias and ensure that all participants allocated to either the intervention (PEERS Plus) or control group are analysed together as representing that ‘treatment arm’ whether or not they received the intervention or completed the study.

Summary statistics will be calculated using means and SD or medians and IQR for continuous measures, depending on data distribution. Ordinal data will be summarised using counts and percentages. The approach to handling missing data will depend on its frequency and the underlying factors contributing to its incompleteness. For example, multiple imputation will be used to address missing data when it is believed to be missing at random. Statistical analysis will be conducted using Stata V.18, while qualitative data analysis will be performed using NVivo V.14.

The primary comparison H1 (attainment of social participation goals) immediately post the intervention at 12 weeks will be based on the COPM and will be between treatment groups using generalised linear models. Analyses will use similar methods to compare the outcomes between groups for secondary outcomes and timepoints (social skills and competence, quality of children’s play, the experience of being bullied and HRQoL).

This study will estimate the costs (both direct and indirect) associated with implementing the PEERS Plus programme. This study will adopt micro-costing/bottom-up approach to estimate the average costs of PEERS Plus groups. This costing study will be conducted from the Australian health system perspective, in which direct consumption of resources for providing the PEERS Plus will be measured. The cost analysis will involve a three-stage process: identifying resource use, measurement and valuation. The intervention cost will include consumables required for providing distinct therapy/interventions under the PEERS Plus and time spent by the trainers/therapists to provide in-person sessions to the adolescents and their caregivers. This information will be valuable to policymakers who need to allocate resources for this evidence-based programme.

